## Abstract

**Background:**

Type 2 diabetes mellitus (T2DM) is a common chronic disease in older adults and a leading cause of death and disability worldwide. While recent diabetes guidelines introduce the Comprehensive Geriatric Assessment (CGA) as a key tool for managing diabetes treatments, evidence of its effectiveness in delaying functional impairment and achieving patient-reported outcomes (PROs) remains lacking. This article describes the protocol of a randomized parallel-group controlled trial aimed at evaluating the effect of a CGA-guided plan of care on physical performance changes over time as compared with a usual-care group.

**Methods:**

Three centers will participate in this study, each recruiting 60 older adults with T2DM from their outpatient clinics. Eligible patients will be randomized into either the usual-care or intervention group in a 1:1 allocation ratio. All patients will receive standard care according to current diabetes guidelines and undergo CGA. For the intervention group, the CGA will guide a multidimensional intervention. Follow-up visits will be scheduled at 6 and 12 months. The primary outcome will be the change in physical performance at the end of the follow-up, as assessed by the Short Physical Performance Battery score, with a comparison between the control and intervention groups.

**Discussion:**

From this study, we will contribute to the growing evidence of the impact of CGA on the assessment and management of older patients with T2DM and its complications. Results will be disseminated through a peer-reviewed journal and presentations at conferences. Final results will be shared with a broader audience through collaborations with patients with diabetes and their caregiver association at local and national levels. The findings will inform the extent to which a CGA-driven care plan may significantly reduce functional impairment and improve patient and caregiver satisfaction.

**Trial registration:**

ClinicalTrials.gov ID: NCT06842459 – registered February 24, 2025 – retrospectively registered.

**Supplementary Information:**

The online version contains supplementary material available at 10.1186/s12877-025-06673-3.

## Background

Type 2 diabetes mellitus (T2DM) is a chronic disease characterized by hyperglycemia, usually due to insulin resistance and progressive loss of insulin secretion or function from the pancreatic β-cells. Globally, the prevalence of T2DM gradually increases with age, exceeding 20% in people over 65 and rising to 25% among those aged 75–79 years [1–3]; indeed, most of the patients with T2DM is 65 and older.

T2DM represents a substantial burden to the healthcare system worldwide [1]. In older patients, it is associated with an increased risk of developing complications due to both macrovascular (e.g., myocardial infarction, stroke, peripheral arterial disease) and microvascular (e.g., retinopathy, nephropathy, and neuropathy) damages [4, 5]. These factors can contribute to multimorbidity and multiple drug prescriptions, leading to an increased risk of adverse clinical events, poor quality of life, and functional loss [5, 6]. Specifically, older patients with T2DM tend to develop disability 6 to 7 years earlier, spend one to two more years with disability, and experience higher rates of premature death (4.6 years earlier) compared to non-diabetic individuals of the same age and sex [7].

In light of these considerations, older patients with T2DM require a comprehensive clinical approach that accounts for multiple variables and outcomes, including relevant patient-reported outcomes (PROs) [8]. Incorporating patient-reported outcome measures (PROMs) and patient-reported experience measures (PREMs) into clinical practice may facilitate identifying patient’s unmet needs and monitoring their evolution over time while improving communication and participation of patients and/or caregivers.

The Comprehensive Geriatric Assessment (CGA) is a validated and effective method for assessing and managing the complex care needs of older patients through goal-driven interventions [9]. Its multidimensional approach, encompassing medical diagnoses, pharmacotherapies, cognitive and physical performance, and environmental and social issues, is essential for developing individualized care plans based on PROMs and PREMs.

The American Diabetes Association (ADA) has recently incorporated elements of the CGA into the standard care of older patients with T2DM, recommending its use to guide therapeutic approaches in T2DM management [10]. However, as these recommendations are still in the early stage of implementation and have not yet become an integral part of routine clinical practice, there is currently no solid evidence supporting the effectiveness of CGA and its associated interventions in delaying functional impairments or achieving key PROs in older adults with T2DM. Our study will address this gap by integrating these outcomes, as part of PROMs, into the care goals of older patients with T2DM.

## Methods/design

### Aims

The primary aim of this study is to evaluate the impact of a CGA-based care planning intervention on physical performance changes of older patients with T2DM, as assessed by the Short Physical Performance Battery (SPPB) [11]. As secondary aims, we will assess the effectiveness of the intervention in reducing the incidence of adverse health outcomes, including falls, sarcopenia, disability, cognitive decline, depression, emergency department admission, hospitalization, institutionalization, and death.

### Study design

This study consists of a multicenter randomized parallel-group controlled trial that will take place at the diabetology outpatient clinics of the University of Cagliari, the University of Ferrara, and the Policlinico di Monza, Italy. Recruitment of the study participants will start in January 2025.

The study protocol was planned in conformity with the Standard Protocol Items: Recommendations for Interventional Trials (SPIRIT) 2025 statement ( Supplementary Table 1) [12].

### Patient screening

All patients attending the diabetology outpatient clinics will be consecutively screened for potential participation in the study.

### Inclusion/exclusion criteria

Eligibility will be determined according to the inclusion and exclusion criteria reported in Table 1.

**Table 1 Tab1:** Exclusion and inclusion criteria

Inclusion criteria	Exclusion criteria
• Age 75 + years • Diagnosis of T2DM • SPPB ≥ 4, indicating none to moderate functional impairment • Ability to understand and speak Italian • Willingness to participate in the study	• Current institutionalization or residence outside the hospital’s catchment area at enrolment • Severe disability, defined as dependence on 3 or more Activities of Daily Living (ADL) • Cognitive impairment or dementia, defined as a MoCA adjusted score < 17.36/30 (ES = 0) • Diagnosis of schizophrenia, bipolar disorder or other psychotic disorders • History of cancer requiring treatment in the past three years, excluding non-melanoma skin cancers and cancers with an excellent prognosis (e.g. e.g. early-stage breast or prostate cancer) • History of cerebrovascular (e.g., ischemic or hemorrhagic stroke, carotid endarterectomy) or cardiovascular accidents (e.g., myocardial infarction, coronary acute syndrome, heart bypass surgery) within the last six months • NYHA Class IV heart failure • Respiratory insufficiency requiring regular supplemental oxygen • Severe chronic kidney disease (e.g. stage V or dialysis or eGFR < 30 ml/min/1,72m^2^) • Decompensated cirrhosis • Alcohol or substances abuse • Inability or unwillingness to provide informed consent • Participation in other trials.

*ADL* Activity of Daily Living, *T2DM* type 2 diabetes mellitus, *eGFR* estimated glomerular filtration rate, *ES* equivalent score, *MoCA* Montreal Cognitive Assessment, *NYHA* New York Heart Association, *SPPB* Short Physical Performance Battery

### Recruitment and randomization

Trained researchers embedded in each diabetology outpatient unit will assess patients for inclusion and exclusion criteria. Those meeting the criteria will be invited to participate and asked to provide written informed consent. After the baseline assessment, participants will be randomly assigned to either the intervention or control group. A secure internet-based system will be used for randomization, assigning participants to the groups in a 1:1 allocation ratio, stratified by center. A total of 60 patients per center will be recruited, for a combined total of 180 participants.

Given the low-risk nature of the intervention, no data monitoring committee has been established for this trial. This approach has been approved by the Ethics Committees at all participating centers.

### Assessment and data collection

Table 2 reports the Gantt charts detailing the timeline and the specialists responsible for the study procedures.

**Table 2 Tab2:** Gantt chart of timeline and specialists

	Recruitment	Baseline	6th months	12th months
Informed consent	○○○○			
Eligibility criteria	○○○○			
Comprehensive Geriatric Assessment		○○○○	○○○○	○○○○
Diabetologist assessment		●●●●	●●●●	●●●●
Randomization		○○○○		
CGA-driven intervention		○○○○	○○○○	○○○○

Legend: ○○○○ Geriatrician, ●●●● Diabetologist

### Baseline assessment

At baseline, all eligible patients will undergo both diabetologist and geriatric assessments. Demographic, clinical, functional, and nutritional data will be collected through CGA by a geriatric researcher at each center, using validated tools [13].

Collected demographic and clinical data are listed in Table 3.

**Table 3 Tab3:** Collected demographical and clinical data

**Demographic** - Age - Sex - Ethnicity - Education - Marital status - Living status - Social support - Economic status	**Clinical** - Height - Weight - Body mass index - Waist circumference - Hip circumference - Brachial blood pressure - Ankle blood pressure - Heart rate - Neurological examination - Peripheral neuro-sensory deficits - Diabetic ulcer - Macrovascular diabetes-related complications - Microvascular diabetes-related complications	**Blood tests** - Complete blood count - Glucose - Hemoglobin A1c - Liver function parameters - Renal function parameters - Albumin - Total proteins - Uric acid

Functional data includes Katz’s Activity of Daily Living (ADL) [14] and Lawton-Brody’s Instrumental Activity of Daily Living (IADL) [15]. Physical performance will be assessed through the Short Physical Performance Battery (SPPB) [11], which evaluates (a) standing balance in three different positions, (b) lower limb strength based on the time taken to stand up from a chair five times as quickly as possible, and (c) gait speed over a distance of 4 m at a normal pace. The SPPB total score ranges from 0 (disability/very poor performance) to 12 points (good performance) [16]. Additionally, upper limb strength will be measured through the grip strength using a held-held dynamometer.

Comorbidity will be assessed using the Charlson Comorbidity Index (CCI) [17]. The Snellen Chart test, the Whispered-voice test, and self-reported screening questions will be used to assess visual and hearing impairment, respectively [18]. Additionally, information on medication use will be obtained through clinical interviews.

Cognitive function will be evaluated using the Italian version of the Montreal Cognitive Assessment (MoCA), with appropriate adjustment of raw score [19, 20]. The MoCA is widely regarded as one of the most effective tools for assessing cognitive function in individuals with normal cognition or mild cognitive impairment. Additionally, depression and anxiety will be screened with a 15-item Geriatric Depression scale (GDS) [21] and 10-item Geriatric Anxiety scale (GAS) [22], respectively.

Nutritional status will be evaluated using the Mini-Nutritional Assessment short form (MNA-sf) and bioelectrical impedance analysis (BIA), while dietary habits through the Mediterranean Score Diet (MSD) [23–25].

The level of frailty will be evaluated using the Primary Care Frailty Index (PC-FI) and the Clinical Frailty Scale (CFS) [26, 27].

Lastly, the quality of life will be evaluated with the 12-item Short Form Health Survey (SF-12) [28].

### Interventions

Every recruited patient will receive standard care in accordance with current diabetes guidelines from a diabetologist. Additionally, a trained geriatric researcher will administer the CGA to patients in both the control and the intervention groups. For the intervention group, the CGA will be used to identify and optimize medical treatment concerning functional outcomes and PROMs. Specifically, the CGA will guide medication review and deprescribing, functional training, nutritional advice, and environmental adaptation. Specialist consultation will be recommended for hearing or visual impairments, and cognitive dysfunction (MoCA ES < 4), or in presence of anxiety or depressive symptoms. Patients in the control group will continue to receive standard care as per current guidelines for patients with T2DM, without additional interventions.

### Follow-up

Follow-up visits will be scheduled 6 and 12 months after randomization and conducted at the diabetology outpatient clinic. For patients unable to attend the outpatient clinics due to incapacity or institutionalization, telephone interviews will be conducted with a relative or caregiver present. For hospitalized patients, an outpatient evaluation will be scheduled post-discharge.

During the in-person follow-up evaluations, data collection will include: height, weight, body mass index (BMI), waist and hip circumferences, brachial and ankle blood pressure, heart rate, peripheral neuro-sensory deficits, diabetic ulcer, macro- and micro-vascular diabetes-related complications, recent blood test results, CCI and pharmacotherapy, ADL and IADL, MoCA, SPPB, handgrip, MNA-sf, BIA, MSD, CFS, PC-FI, 15-item GDS and 10-item GAS, SF-12, social support, and living situation, fall occurrences, and hospitalization rates. During telephone interviews, the following data will be collected: self-reported weight, home-measured brachial blood pressure, recent blood test results, CCI and pharmacotherapy, MNA-sf, ADL and IADL, 15-item GDS and 10-item GAS, social support, and living situation, fall occurrences, and hospitalization rates. Lastly, follow-up assessment will include patients’ experience with care, including perceived involvement in treatment decision, clarity of information received, coordination among healthcare professionals, and the perceived value of diabetes self-management education.

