### Sample size and statistical analysis

Using data from a previous observational study in older Italian patients with diabetes [29], we hypothesized a baseline mean SPPB score of 6.9 with a 1.8 standard deviation. Assuming that a difference of 1 SPPB score point is clinically meaningful [30], we estimated that 72 patients in each group would provide a 90% power at a 5% significance level to detect this difference between the intervention and the control group after 12 months from enrolment. To account for a 20% loss to follow-up, including patients who will die during the study follow-up, we planned to enroll 90 patients for each study group, for a total of 180 participants.

Data will be described as mean and standard deviation or median and interquartile range for continuous variables and frequency and percentage for categorical variables. Baseline characteristics will be compared between intervention and control groups using ANOVA for normally distributed continuous variables, nonparametric tests for non-normally distributed continuous variables, and chi-square or Fisher’s exact test for categorical variables.

Changes in SPPB scores (primary outcome) between study groups over follow-up will be assessed using longitudinal data analysis for repeated measures. Differences in secondary binary outcomes between groups will be analyzed using multivariable logistic regression models or Cox proportional hazard models, as appropriate. Changes in secondary continuous outcomes between groups will also be evaluated using longitudinal data analysis for repeated measures. All statistical models will be adjusted for relevant potential confounders, including socio-demographic factors, comorbidities, medications and study center. Confounders will be selected based on their association with the specific outcome being analyzed and consideration of collinearity. Comorbidities and medications will be incorporated into the models either as individual variables - when specific conditions or treatments are expected to influence the outcome - or as aggregated measures (e.g., total number of comorbidities or medications) to reflect overall disease or treatment burden, depending on their distribution and relevance. A two-tailed p-value < 0.05 will be considered statistically significant.

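### Telephone follow-up omits the SPPB and the reason it was not done, so primary-outcome data are missing for reasons tied to function

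*Protocol article*

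**What the plan says.** The primary outcome is change in SPPB at the end of follow-up, compared between groups (Outcomes). Visits are at 6 and 12 months in the diabetology clinic. The exception is stated under Follow-up: "For patients unable to attend the outpatient clinics due to incapacity or institutionalization, telephone interviews will be conducted with a relative or caregiver present". Hospitalized patients are seen as outpatients after discharge.

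Follow-up gives two data lists. The in-person list includes the SPPB and handgrip. The telephone list keeps ADL, IADL, mood scales, nutrition, falls and hospitalization, among others, but has no SPPB and no entry for why it was not done. The article describes no home or institution visit.

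Baseline assessment describes the scale: "The SPPB total score ranges from 0 (disability/very poor performance) to 12 points (good performance".

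Sample size and statistical analysis allows for attrition: "To account for a 20% loss to follow-up, including patients who will die during the study follow-up". It analyses SPPB change by longitudinal analysis for repeated measures.

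ADL disability, institutionalization, mortality and days at home are secondary outcomes, and the Discussion calls the analyses of secondary outcomes exploratory.

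**The concern.** A patient is moved to the telephone because of incapacity or institutionalization. Both are plausible consequences of the functional decline that the SPPB measures, and the Discussion expects the intervention to prevent or delay disability. The chance that a score is missing is therefore likely to depend on the score that would have been obtained.

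A likelihood-based repeated-measures model handles missing scores correctly if, given the observed data, missingness does not depend on the unseen value. A patient who was testable at 6 months and then lost function would be predicted from the better earlier scores. If this happens more often in one arm, the estimated effect is biased.

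The data collection matters more than the model. A statistical analysis plan can set scoring rules and sensitivity analyses later. It cannot recover a reason for non-testing, or a record of whether the patient could stand and walk, that nobody wrote down.

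**Working it through.** **1. The plan's own figures.** Inputs from Sample size and statistical analysis: "we hypothesized a baseline mean SPPB score of 6.9 with a 1.8 standard deviation"; a target difference of 1 point; "72 patients in each group would provide a 90% power at a 5% significance level"; two-sided testing.
- Normal approximation: n = 2 × 1.8² × (1.960 + 1.282)² / 1² = 68.1, so 69 per group. The two-sample t-test gives 70. Dividing 68.1 by the Wilcoxon efficiency 3/π gives 71.3, so 72.
- Power with 72 per group is 0.915 (normal approximation) or 0.912 (t-test).
- 72 / 0.80 = 90 per group, 180 in total. The allowance is 0.20 × 180 = 36 patients, for losses of all causes.

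The sample size is sound on its inputs. The inflation protects the number of scores, not their representativeness.

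**2. Missingness that depends on the score.** The article gives no rates, so everything here is assumed: SD 1.8, a true 12-month difference of 1 point, baseline-to-12-month correlation 0.6 to 0.8, and SPPB unmeasured when it falls below a cut.

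Analysis of measured patients adjusted for baseline only (12-month means 6.4 control, 7.4 intervention):

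| Cut | Missing, control v intervention | Estimate of a true 1.00 |
|---|---|---|
| below 3 | 3% v 1% | 0.94 to 0.97 |
| below 4 | 9% v 3% | 0.86 to 0.92 |
| below 5 | 22% v 9% | 0.74 to 0.84 |

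Missing-at-random likelihood-type estimate that also uses 6-month scores (effect at 6 months half as large):

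| Cut | Missing, control v intervention | Estimate of a true 1.00 |
|---|---|---|
| below 4 | 5–7% v 2–3% | 0.91 to 0.96 |
| below 5 | 16–20% v 7–10% | 0.83 to 0.89 |

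The second table has less missingness than the first at the same cut, so the two do not measure how much the 6-month score helps. They show that attenuation remains when it is used. Over cuts 4 and 5 the estimates run from 0.74 to 0.96. That range describes these scenarios and is not a bound.

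**3. Scoring inability or death as 0.** This changes the question from the effect among those measured to the effect among all randomised. With mean 6.9 in measured controls, difference d among the measured, and non-assessable shares m_C and m_I (assumed):

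Δ = (1 − m_I)(6.9 + d) − (1 − m_C) × 6.9

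| m_C | m_I | d | Δ |
|---|---|---|---|
| 10% | 10% | 1 | 7.11 − 6.21 = 0.90 |
| 20% | 10% | 1 | 7.11 − 5.52 = 1.59 |
| 10% | 15% | 1 | 6.715 − 6.21 = 0.505 |
| 20% | 10% | 0 | 6.21 − 5.52 = 0.69 |
| 10% | 15% | 0 | 5.865 − 6.21 = −0.345 |

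With equal shares the change is small. With unequal shares it can be large, in either direction.

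**4. Spread if zeros enter a comparison of means.** With 5% zeros: SD = √(0.95 × 1.8² + 0.05 × 0.95 × 6.9²) = √(3.078 + 2.261) = 2.31. At 90 per group, power for a 1-point overall difference in means is then 83%. This figure belongs to a comparison of means, not to the rank test proposed under the fix.

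**The case against.** The strongest reply is that most of this belongs in the statistical analysis plan. How to score inability, how to treat death and which sensitivity analyses to run are commonly settled there, and a condensed article that is silent on them is not wrong. That stands. What does not depend on the unseen plan is the telephone data list, which the article spells out.

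A reader might go further and infer that the trial ignores its worst functional outcomes. The article does not support this, for five reasons:
- Baseline and any 6-month SPPB can still enter a repeated-measures model, and hospitalized patients are tested after discharge.
- ADL and IADL are collected by telephone, so function is not unrecorded.
- SPPB after death is undefined; it is not a score left uncollected by design. The attrition sentence is a sample-size allowance, not an analysis rule for deaths.
- Mortality, institutionalization, ADL disability and days at home record these events, although only as secondary outcomes.
- Entry criteria exclude SPPB below 4, institutionalization and dependence in three or more ADL, which may limit how many patients are affected.

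A reader might also infer that a real benefit would vanish from the primary estimate. The outcome-dependent scenarios show attenuation, not disappearance. The larger movements in step 3 are a change of estimand under assumed rates, not a bias demonstrated in the plan.

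**Conclusion.** The point holds in a limited form. For patients followed by telephone because of incapacity or institutionalization, the primary outcome is not collected at that visit, for a reason tied to the outcome, and the listed data do not say why. An analysis that assumes missingness at random is open to bias in that setting.

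Neither size nor direction can be derived from the article. The attenuation in step 2 rests on assumed cuts, correlations and means, with a real effect present. The 36 patients are a planning allowance for all losses, not an estimate of the number incapacitated, institutionalized or dead. I would class this as a cheap improvement rather than a must-fix error: the primary model and the sample size need not change.

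**What to change.** 1. Add to the telephone form the reason the SPPB was not done, and whether the patient can stand, rise from a chair and walk. Do this while follow-up is still running.
2. Report non-assessable patients and deaths by arm and reason.
3. Keep the repeated-measures model as the primary analysis.
4. Unless the statistical analysis plan already does so, pre-specify one supporting analysis of 12-month SPPB. Patients alive but physically unable to do the test score 0, in line with the scale's own lowest anchor. Deaths rank below all survivors. The arms are compared by a rank-based test stratified by centre, as the randomization is. Patients not tested for other reasons should not be given a 0, which is why item 1 is needed.
5. State in advance that, if the two analyses disagree, the primary conclusion is limited to patients alive and able to be tested.

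The cost is a few telephone items, often answered with a relative or caregiver present, and one extra analysis. The power of that analysis has not been computed, so what counts as disagreement should be defined beforehand; a non-significant result in the same direction should not count by itself.
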